### Clinical follow-up

Death, reinfarction, and ischemia driven target-vessel revascularization are to be registered at 30 days and 1 year. Follow-up information will be obtained from the central personal records database, hospital records as well as by telephone interviews with the patients and/or their general practitioners.

### Statistical considerations

#### Sample size estimation

In previously published data, the incidence of our primary end point resolution of ST-segment elevation >70% has been reported to be 56.6% in patients with STEMI treated with thrombus aspiration [11]. We hypothesize that IC administration of abciximab during PCI increases the incidence of ST-segment resolution >70% by 25%. To detect a 25% difference between the two treatment groups, 530 patients are required to reach a 5% significance level (two-sided) with 90% power.

#### Statistical analysis

All statistical analyses will be performed according to the intention-to-treat principle for the overall population as well as for the pre-specified subgroups. Statistical significance is considered as a two-tailed p value less than 0.05. The Statistical Package for the Social Sciences (SPSS Inc., Chicago, IL, USA) version 16.0.2 will be used for all statistical analyses. Differences between group means will be assessed with the two-tailed Student's t-test. Chi-square analysis or Fisher's exact test will be used to test differences between proportions. Survival will be calculated by the Kaplan-Meier product-limit method. Chi-square analysis will be used to assess the relation between an individual variable and end points. The Mantel-Cox (or log-rank) test will be used to evaluate differences in survival between the two treatment groups. The Cox proportional-hazards regression model will be used to calculate relative risks and to adjust for differences in baseline characteristics.

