### End points assessment

The primary end point is the incidence of ST-segment resolution >70% as assessed on the ECG acquired 30 to 60 minutes after PCI compared to the ECG at presentation.

Secondary end points include:

- Angiographic end points: post-procedural TIMI flow, MBG (by visual estimation and with the QuBE program) and angiographically visible distal embolization

- Electrocardiographic end points: residual ST-segment deviation 30 to 60 minutes after the procedure

- Enzymatic infarct size

- Mortality and Major Adverse Cardiac Events (MACE, a combined end point of target vessel revascularization, reinfarction, and cardiovascular mortality) at 30 days and 1 year.

A safety endpoint consists of in-hospital bleeding complications.

Furthermore, the primary and secondary endpoints are to be analyzed in pre-specified subgroups, which are defined as:

1. Age (<65 versus >65 years)

2. Gender

3. Presence of diabetes

4. Number of diseased vessels (multi-vessel versus single vessel)

5. Infarct-related artery (left anterior descending artery (LAD) versus non-LAD)

6. Ischemic time (<3 versus >3 hours)

7. Angiographic presence of thrombus

8. Pre-procedural TIMI flow

9. Post-procedural TIMI flow

10. Post-procedural myocardial blush grade

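### The plan applies p<0.05 across ten subgroup factors and names no method that compares effects between levels, so nominally discordant subgroup results are likely even if the effect is uniform

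*Protocol article*

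**What the plan says.** Three statements in the protocol article fix the subgroup analysis.

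- **Scope.** End points assessment: "the primary and secondary endpoints are to be analyzed in pre-specified subgroups, which are defined as". Ten factors follow. The first is "Age (<65 versus >65 years", the sixth splits ischemic time the same way at 3 hours, and the last is "10. Post-procedural myocardial blush grade".
- **Population and threshold.** Statistical analysis: "All statistical analyses will be performed according to the intention-to-treat principle for the overall population as well as for the pre-specified subgroups", followed by "Statistical significance is considered as a two-tailed p value less than 0.05". The threshold does not distinguish overall from subgroup results.
- **Methods.** Student's t-test for means, then "Chi-square analysis or Fisher's exact test will be used to test differences between proportions", then Kaplan-Meier and log-rank for survival. The only regression model is introduced as follows: "The Cox proportional-hazards regression model will be used to calculate relative risks and to adjust for differences in baseline characteristics". No interaction term is mentioned, and no model is named that could carry one for the binary primary end point.

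**The concern.** If two-group tests are the only tools and they are applied to subgroups, the natural reading is that they are run inside each level. A significant result in one level and a non-significant one in the other does not show that the effect differs. Each level holds fewer patients than the trial was sized for, and chance alone separates the two p values. With ten factors and many end points under one 0.05 threshold, some nominally positive levels are also to be expected when there is no effect at all.

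The list has two further faults. Factors 9 and 10 (post-procedural TIMI flow and blush grade) are measured after treatment and are themselves secondary end points. The cut-points for age and ischemic time leave a patient at exactly 65 years or 3 hours in neither level.

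The interpretation of subgroup results is at stake. The overall test of the primary end point is not affected.

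**Working it through.** **Inputs from the article (Sample size estimation, End points assessment).** Control rate 56.6%; a 25% increase, read as relative: 0.566 × 1.25 = 0.7075; N = 530; two-sided 5%; 90% power; ten factors.

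**Assumptions.** 1:1 allocation (265 per arm); two levels per factor; factors independent of each other; same control rate in every level. The article gives no level shares. Three sets were used: ten factors split 50/50; ten factors with 12-50% of patients in the smaller level; and the eight baseline factors with shares of 12-70% in one level.

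**1. The plan's own figure.** Let d = p₁−p₀ = 0.1415, A = √(2p̄q̄) = 0.680 with p̄ = 0.63675, and B = √(p₁q₁+p₀q₀) = 0.673.

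n per arm = (1.960·A + 1.282·B)² / d² = 2.195² / 0.0200 ≈ 241, so 482 in total (510 with continuity correction). The stated 530 is not reproduced. An unstated 10% allowance would give it (241 × 1.10 ≈ 265 per arm). An absolute increase of 25 points would need only 140, so the relative reading is kept. At 265 per arm the overall power is 92.5%. The mismatch does not bear on this point.

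**2. Power inside a level holding share s of patients.** Power = Φ[(d·√(265s) − 1.960·A)/B]

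| Share s | Power |
|---|---|
| 0.90 | 90% |
| 0.75 | 84% |
| 0.50 | 67% |
| 0.25 | 39% |
| 0.12 | 21% |
| 0.10 | 18% |

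**3. Discordance for one factor, uniform planned effect.** With powers a and b in the two levels, the chance that exactly one is significant is a(1−b) + b(1−a).

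- 50/50: 2 × 0.670 × 0.330 = 44%
- 75/25: 0.837 × 0.606 + 0.394 × 0.163 = 57%
- 90/10: 0.897 × 0.816 + 0.184 × 0.103 = 75%

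Unequal size makes discordance worse, but it already reaches 44% when the levels are equal.

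**4. At least one discordant factor.** All factors divide the same 530 patients, so the single-factor figures cannot be multiplied; 3,000-4,000 trials were simulated instead. Results: 85% (ten factors, equal splits), 95% (eight baseline factors) and 97% (ten factors, unequal splits).

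**5. No effect anywhere, primary end point.** Treating the levels as independent gives 1 − 0.95²⁰ = 64% for ten factors. Allowing for shared patients, the simulated chance of at least one p<0.05 is 42-43% for ten factors and 39% for the eight baseline factors.

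**6. All end points, no effect.** Counting eleven (ST resolution; TIMI flow; visual blush; QuBE; distal embolization; residual ST deviation; infarct size; mortality and MACE at two times each) gives 11 × 20 = 220 tests and 220 × 0.05 = 11 expected nominal positives. The simulated chance of at least one runs from 87.5% (assumed correlation 0.8 between end points) to 99.7% (uncorrelated).

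**7. The same check with interaction tests.** For eight tests at 0.05, 1 − 0.95⁸ = 34%; simulation under the uniform planned effect gives about 32%. At 0.05/8 = 0.00625 each, 1 − 0.99375⁸ = 4.9%. For the eight baseline factors, misleading patterns under a uniform effect thus fall from 95% to about 32%, but the no-effect rate moves only from 39% to about 34%.

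**8. Factors 9 and 10.** The secondary end point list includes post-procedural TIMI flow and blush grade; so does the subgroup list. Taken literally, blush grade is to be analysed within levels of blush grade. Since treatment may change both measures, patients in the same post-procedural grade are no longer a randomized comparison, and an interaction test does not restore it.

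**The case against.** The best defence is that a condensed article may leave the interaction test, the exploratory label and multiplicity to a full protocol or SAP that is not shown. Their absence alone would not be a finding. That stands, so the point rests on what the article does fix: scope, tests and threshold, which together form a rule that misleads if followed.

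Second, within-level testing is the natural reading of these sentences, not their literal text. That also stands.

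Third, a reader might infer that false or discordant subgroup claims are close to certain. The documents do not support this. Nowhere does the article say that a subgroup claim will rest on a within-level p value, and the stated objective concerns the overall comparison. The no-effect figure for the primary end point is about 40%. The 85-97% figure needs the full planned effect in every patient, so the two scenarios cannot both hold.

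Fourth, interaction tests at 0.05 hardly lower the no-effect error (step 7). This is correct, and is why the remedy must do more than swap one test for another.

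**Conclusion.** The point holds in this limited form. The article applies two-group tests at a single 0.05 threshold to ten subgroup factors for the primary and all secondary end points, and names nothing that compares effects between levels. On the natural reading, nominally discordant results are likely under a uniform planned effect (about 85-97%), and a nominally significant level arises in about 40% of trials with no effect on the primary end point.

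These sizes depend on the assumed level shares, independent factors, binary splits and 1:1 allocation. The faults in factors 9 and 10 and in the two cut-points follow from the text alone and need no assumption. Since the primary overall analysis is untouched, this should be corrected but does not threaten the trial's main conclusion.

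**What to change.** - For the eight baseline factors, replace within-level significance tests by one treatment-by-factor interaction test each, on the primary end point only, using logistic regression.
- Show level-specific effects with 95% CIs, for example in a forest plot, without within-level p values.
- Label these analyses exploratory and state how many interaction tests are done. Either acknowledge the remaining chance of about 34% of at least one false interaction, or use a Bonferroni threshold (0.05/8 = 0.00625).
- Remove post-procedural TIMI flow and blush grade from the treatment-effect subgroups and keep them as secondary end points.
- Close the cut-points so that every patient falls in one level, for example <65 versus ≥65 years and <3 versus ≥3 hours.

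The cost is wording and a few model terms in software already named. The downsides are the low power of interaction tests, lower still under Bonferroni, and the residual false-interaction rate if 0.05 is kept.

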### Electrocardiography

A standard 12-lead electrocardiogram (ECG) is acquired at the time of presentation and at 30 to 60 minutes after the end of procedure. Times of onset of symptoms, admission, first intracoronary intervention, end of PCI and ECG recordings are registered. The magnitude of ST-segment deviation is measured 60 ms from J-point. The first post-intervention ECG at 30 to 60 minutes is classified by comparison of the ST-segments with those of the ECG at presentation. ST-segment elevation resolution is categorized as complete (>70%), partial (30-70%), or absent (<30%) [6]. On the post-interventional ECG, residual ST-segment deviation is calculated as the sum of residual ST-segment elevation and depression in all leads [37]. New-onset of Q waves on the post-interventional ECG is defined as an initial negative deflection of the QRS complex of >0.1 mV and >40 ms in an ECG lead related to the myocardial area of infarction together with all pathological Q waves. All ECG recordings are analyzed by a physician blinded to treatment allocation and clinical data.

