### Infarct size

Infarct size is estimated by serial measurements of cardiac markers including creatinine kinase (CK), myocardial band fraction of CK (CK-MB), lactate dehydrogenase (LDH), and troponin T. Blood is sampled at baseline and at 3, 6, 9, 12, 18, 24, and 48 hours after PCI. Peak release, time to peak release as well as area under the curve is determined. Marker levels are determined on a Hitachi 717 automatic analyzer according to the International Federation of Clinical Chemistry (IFCC) recommendation.

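### Continuous secondary end points get only an unadjusted t-test, which is valid but probably inefficient, and enzymatic infarct size has no lead measure among eight candidates

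*Protocol article*

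**What the plan says.** - **Test.** Statistical analysis: "Differences between group means will be assessed with the two-tailed" Student's t-test. No rank test, transformation or covariate-adjusted model is named for continuous outcomes.
- **Threshold.** Same section: "Statistical significance is considered as a two-tailed p value less than 0.05". No order of importance is given among the secondary measures.
- **Covariates.** Same section: "The Cox proportional-hazards regression model will be used to calculate relative risks and to adjust for differences in baseline characteristics". That model serves time-to-event outcomes.
- **Enzyme end point.** End points assessment has the single entry "Enzymatic infarct size". Infarct size bases the estimate on "serial measurements of cardiac markers including creatinine kinase (CK), myocardial band fraction of CK (CK-MB), lactate dehydrogenase (LDH), and troponin T", and continues: "Peak release, time to peak release as well as area under the curve is determined". The sampling schedule is given ("Blood is sampled at baseline and at 3, 6, 9, 12, 18, 24, and 48 hours after PCI"), but no marker or summary is put first.
- **Residual ST deviation.** Electrocardiography: on the post-procedural ECG, "residual ST-segment deviation is calculated as the sum of residual ST-segment elevation and depression in all leads". The same section has a standard 12-lead ECG recorded at presentation. The primary end point uses that ECG, but the comparison of residual ST deviation does not.

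**The concern.** There are two separate issues.

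**Choice of test.** Enzyme peaks and areas cannot be negative, and residual ST deviation is a sum bounded at zero. Variables of this kind are often right-skewed. A comparison of arithmetic means then depends heavily on a few large values and can miss a real proportional difference that a log-scale or rank analysis would detect. For residual ST deviation, the presentation ECG supplies a natural baseline covariate at no extra cost, and the named test cannot use it.

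**Definition of the end point.** One label covers several measures, each of which could be judged at 0.05. A chance difference in any of them could be reported as a smaller infarct, and the choice could be made after the results are known.

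At stake are the sensitivity and credibility of secondary evidence on infarct size and reperfusion.

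**Working it through.** **The plan's own figures.** The article gives no SD, skewness, correlation or power for these end points. Its only sample size figure, 530, is for the primary end point. Reading the 25% increase as relative (56.6% against 70.75%, two-sided 5%, 90% power), the usual formula gives 482, or 510 with continuity correction. So 530 is not reproduced exactly, but it lies on the safe side and has no bearing here. I take 265 per arm, assuming 1:1 allocation because the ratio is not stated.

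**1. Counting the measures.** Four markers × two size summaries (peak, area) = 8. Four markers × time to peak = 4 timing measures. Total 12.

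**2. Is the t-test valid?** Simulation with log-normal data, no treatment effect, 265 per arm, 4000 runs and log-SD 0.5 to 1.5 gave a type I error of 3.6% to 5.2% for the t-test on the original scale. It is valid.

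**3. Efficiency and power under assumed log-normal values.** For a coefficient of variation CV:
- log-scale variance σ² = ln(1 + CV²)
- efficiency of the original-scale test = σ²/CV²
- for a ratio of 0.8, z(log) = |ln 0.8| / √(2σ²/265)
- z(original) = 0.2 / [CV × √((1 + 0.8²)/265)]
- power = Φ(z − 1.96)

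| CV (assumed) | σ² | Efficiency | z(log) | Power, log | z(original) | Power, original |
|---|---|---|---|---|---|---|
| 0.7 | 0.399 | 81% | 4.07 | 98% | 3.63 | 95% |
| 1.0 | 0.693 | 69% | 3.09 | 87% | 2.54 | 72% |
| 1.25 | 0.941 | 60% | 2.65 | 75% | 2.03 | 53% |

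Simulation agrees in direction. Where the log-scale test has about 80% power, the original-scale t-test has about 75% at log-SD 0.5, 67% at 0.8 and 57% at 1.0. The rank test keeps 77% to 79%.

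**4. Baseline adjustment of residual ST deviation.** With correlation r between presentation and residual deviation, the variance is multiplied by 1 − r². At r = 0.3 this is 0.91 (a 9% cut); at r = 0.5 it is 0.75 (a 25% cut). A comparison with 80% power unadjusted would have Φ(2.80/√(1 − r²) − 1.96), which is 83.6% and 89.9%. At r = 0.1 it would be only 80.4%.

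**5. Chance of at least one p < 0.05 when no measure differs.** If independent, this is 1 − 0.95^k: 34% for k = 8 and 46% for k = 12. For equally correlated measures (correlation assumed):

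| Correlation | 8 size measures | All 12 |
|---|---|---|
| 0.5 | 25% | 32% |
| 0.7 | 19% | 23% |
| 0.9 | 12% | 13% |

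**The case against.** The case on the other side is substantial.

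- **Scale.** A reader might infer that the article prescribes analysis of untransformed values. It neither says so nor rules out a transformation. A condensed article may leave scale and sensitivity analyses to an analysis plan that is not shown. This stands: silence on transformation is not the point. What remains is that a test is named, that it is the only one for continuous outcomes, and that a better one is available.
- **Validity.** A reader might infer that the t-test would give false results. It would not. Its error rate holds at this size, and an unadjusted comparison of randomised arms is unbiased.
- **Size of the loss.** The documents support no particular figure. Assuming log-normality favours the log-scale test by construction, and at CV 0.7 the difference is 95% against 98%, which is small. This stands, so the loss can only be given as a range.
- **Estimand.** A log-scale analysis estimates a ratio of geometric means rather than a difference in arithmetic means. That is a real change, though a reasonable one for marker release.
- **Number of measures.** A reader might count twelve infarct-size end points. Time to peak measures timing, so eight is the fair count. The article does not say that each will be a separate claim. The markers are probably closely correlated, which favours the lower percentages.
- **Reach.** A reader might extend the selection problem to residual ST deviation, or ask for baseline adjustment of the enzyme measures. Residual ST deviation is a single defined quantity. Baseline blood is sampled, but nothing in the article shows how much it would predict later release.

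The objection does not answer the missing lead measure. What a listed end point consists of is a matter for the protocol, and the same article defines residual ST deviation fully.

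**Conclusion.** The point holds as one about efficiency and definition in the secondary end points, not as an error of validity.

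- **Definition.** This part needs no distributional assumption: one label, eight size measures, no lead measure. The chance of at least one false positive is about 12% to 25% for the eight at assumed correlations of 0.9 to 0.5, against a nominal 5%.
- **Efficiency.** The named test is probably inefficient for enzyme peak and area, with 81% to 60% of the efficiency of a log-scale test at assumed CVs of 0.7 to 1.25. For residual ST deviation, leaving out presentation ST deviation forgoes a variance cut of 9% to 25% at assumed correlations of 0.3 to 0.5. Both ranges depend on quantities that the article does not give, and the gain could be small.

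The primary end point, its test and the sample size are untouched.

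**What to change.** 1. Name one marker and one summary as the enzymatic infarct size end point, for example CK-MB area under the curve to 48 hours. Label the other measures supportive, with time to peak described as timing.
2. Analyse enzyme peak and area under the curve on the log scale. Report geometric mean ratios with 95% confidence intervals, with a Wilcoxon rank-sum test as sensitivity analysis.
3. Analyse residual ST deviation in a linear model with treatment and summed presentation ST deviation as terms, on a log(x + constant) or rank scale if skewed. State that the presentation sum is derived in the same way as the post-procedural one.

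The cost is a change of wording before the data are unblinded, plus reading the summed deviation from the presentation ECG. The ECGs, blood samples and software stay the same. The small downside is that enzyme effects appear as ratios rather than mean differences; arithmetic means can still be tabulated by arm.

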## Discussion

The CICERO trial is a single-center, prospective, randomized trial to determine whether IC administration of abciximab during primary PCI is more effective than IV administration in improving myocardial perfusion in STEMI patients undergoing primary PCI with thrombus aspiration. This is the first large clinical trial to date to determine the effect of IC versus IV administration of abciximab in STEMI patients undergoing primary PCI with thrombus aspiration.
